### Recruitment and randomisation

Recruitment is through self-selection with LftW verification. LftW circulated calls to apply for the InBusiness programme in the eight counties where it will be operating in. Individuals submitted an application, and LftW verified if they meet eligibility criteria.

LftW has funding to provide the programme to approximately 480 people across two cohorts (cohort 1: enrolment in March 2023 and cohort 2: enrolment in March 2024). LftW verified 776 eligible people between December 2022-February 2023. Within this group, individuals will be randomised to either cohort 1, cohort 2 or the control group (Fig. 1). The RCT will focus on cohort 1 (intervention group) and the control group. Cohort 2 will not be part of the RCT as they will not have been involved in the project for sufficient time at follow-up.

Randomisation will take place in two phases. Individuals will first be randomised to either cohort 2 or the group taking part in the RCT. Baseline data will then be collected from the RCT group, after which individuals will be randomised to cohort 1 or the control group. Randomisation will be within counties based on quotas from LftW on the number of placements available for cohorts 1 and 2, and each group will be roughly balanced by gender. Randomisation will be done through R by staff at the London School of Hygiene & Tropical Medicine (LSHTM).

If there are a small number of dropouts in people randomised to cohort 2 (< 20 individuals), LftW can recruit from the control group to avoid needing to re-advertising and re-verifying applicants. In this instance, individuals moving from control to cohort 2 will be selected randomly and will be excluded from the analysis.

**Fig. 1 Fig1:**
[figure not shown]
Flow diagram of recruitment and randomisation

For the qualitative research and process evaluation, 20–25 participants will be recruited from the RCT group prior to endline (predominantly people in cohort 1, with some from the control arm). Recruitment will be purposive to maximise heterogeneity by gender, impairment type, location, type of microenterprise and if the microentrepreneur (ME) is a caregiver or a person with a disability. Additionally, 15–20 InBusiness programme implementers and key partners will be selected based on their involvement in different stages of InBusiness design and delivery.

### Intervention

The InBusiness programme seeks to improve the social and economic wellbeing of MEs with disabilities and their households. The programme primarily targets people with disabilities who are the primary owner of a microenterprise but in a minority of cases will offer the programme to businesses run jointly by a people with disabilities and a caregiver or businesses run only by a caregiver of an adult/child with a disability. The programme provides business, technical, self-advocacy and compliance skills training and in-kind transfers of assets required to expand the business named “business growth kits” and facilitates procurement opportunities with PPIs.

The InBusiness programme will be delivered over 10 months. The core components include the following:Classroom-based trainings: Microentrepreneurs will receive classroom training on skills to improve their business practices. Content covered in trainings includes record keeping, compliance with national and local regulations and self-advocacy.Capacity building: One-to-one follow-up with microentrepreneurs to monitor their progress and implementation of trainings and to offer tailored advice to support their businesses.Business growth kits: Microentrepreneurs will be provided with an in-kind asset to grow or improve the profitability of their business and/or support their participation in the business (e.g. assistive products). The asset will be tailored based on the needs of each microentrepreneur’s business and/or accessibility needs.PPI disability inclusion training: PPIs will be trained on disability inclusion and encouraged to offer procurement opportunities to people with disabilities (e.g. through the access to public procurement opportunities programme).Linking to procurement opportunities: Microentrepreneurs will be made aware of and supported to apply for procurement opportunities with local PPIs.

### Usual care

Microentrepreneurs in the control arm will receive usual care, meaning they will not be offered enrolment to the InBusiness programme during the duration of the trial. However, they are free to use any services or programmes operating in their area. They will be compensated for their participation in the study and offered information about available social protection programmes (e.g. procurement quotas for people with disabilities) and on compliance with local/national laws related to microenterprises.

### Data collection

Data for the RCT will be collected using questionnaires completed by participants in the intervention and control arms at baseline and endline. Data collection will be conducted in a place of the participants’ choosing (e.g. home, business). The questionnaire is based upon standard modules and from modules used in other studies (Table 1). It includes sections on the following: household composition, housing conditions, food security, savings and expenditures; individual economic empowerment, well-being and access to services; and microenterprise revenues, costs and practices. It was reviewed by programme implementers and piloted with individuals who had previously participated in the InBusiness programme to check for acceptability and understanding before full-scale data collection. The survey will take approximately 1 h to complete and will be delivered by trained enumerators using Open Data Kit (ODK).

**Table 1 Tab1:** Outcome indicators for the RCT of the InBusiness programme

Outcome indicator	Description	Source
*Primary outcomes*		
Household consumption	Overall per capita household consumption and domains of expenditures (food, health) adjusted for inflation	Adapted version of [14]
Economic empowerment	Score on a 14-item financial self-efficacy tool	Adapted version of [15]
*Secondary outcomes*		
Subjective wellbeing	Total score on a 7-item tool on self-reported well-being	Adapted version of [16]
Food security	Proportion classified as facing moderate or severe food insecurity	Food Insecurity Experience Scale [17]
Social attitudes	Total score on 9-item tool on social attitudes	World Health Model Disability Survey [18]
Unmet need for disability-related goods and services	Self-reported unmet need for disability-related healthcare, assistive devices or assistance	Tool developed for study
Microenterprise profits	Net of revenues minus costs, adjusted for inflation	Tool developed for study

In-depth interviews will be conducted with 20–25 participants of the RCT at endline and with 15–20 programme implementers as part of the process evaluation. Interviews will use semi-structured topic guides and will be conducted by experienced researchers. They will be recorded, transcribed and, where needed, translated to English. Interviews with RCT participants will focus on barriers and enablers to running microenterprises. The InBusiness programme participants will also be asked about the perceived impact of the programme, the strengths and areas for improvement in different components to the programme and any recommendations for adapting the overall programme. Interviews with implementers will focus on their experience developing and/or delivering the components of InBusiness they were responsible for, including any challenges, adaptations and suggestions for improvements.

### Outcomes

A theory of change was created in collaboration with programme implementers to identify anticipated outcomes of the InBusiness programme. The ultimate aim of InBusiness is to improve the livelihoods of microentrepeneurs of people with disabilities and their households, which can lead to reduced poverty and improved well-being. The primary outcome measure is changes in household expenditures and economic empowerment (Table 1). Secondary outcome measures will include subjective well-being, food security, social attitudes, unmet need for disability-related goods and services and microenterprise profits. Indicators are tied to the existing tools where possible.

The endline survey will also collect information from the intervention arm about their experience participating in the programme, including the following: (a) details on receipt of different components of the intervention to explore fidelity and uptake (e.g. what was received, frequency, how delivered), (b) satisfaction with the programme overall and with specific components, (c) challenges experienced during any component of the intervention, and (d) self-reported impacts of participation.

### Sample size

One of primary outcome measures is household expenditure per capita. Using data from the Kenya Integrated Household Budget Survey (KIHBS) 2015/2016 [19], we assume an average household per capita expenditures of 7811 KSH. Standard deviation was not presented in the report, but we assume standard deviation of 40% of the mean (3124 KSH). With power of 80% and type 1 error of 5%, we would need a total sample size of 398 (199 per arm) to detect an effect change of 10% of household expenditure per capita. Assuming a loss to follow-up of 20% and a potential switch of 20 individuals from control group to cohort 2 (excluded from RCT analysis), we will need to recruit at least 497 individuals.

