## Methods and analysis

### Design

The study’s main design is an individual, superiority RCT of the LftW-led component of the InBusiness programme.^1^ It follows the SPIRIT guidelines for RCTs (Supplemental file 1). The LftW InBusiness programme is being implemented in 8 of 47 counties in Kenya. Individuals applying to InBusiness will be randomised to either the intervention or control group. The intervention group will be offered a place on the InBusiness programme for enrolment in March 2023. The control group will not be offered a place on the InBusiness programme but will receive information about compliance with business laws and on available social protection programmes. Baseline data collection will be conducted before randomisation and before participants are invited to enrol in InBusiness to minimise anticipatory behaviour. Follow-up will be conducted 24 months after baseline (12 months after the completion of the delivery of InBusiness).

The RCT will be complemented with a process evaluation and qualitative research. In-depth interviews will be conducted with participants in both study arms after the delivery of InBusiness is completed to explore their experiences of running a microenterprise, and for the intervention arm, and of participating in the InBusiness programme. In-depth interviews with programme implementers will also be conducted, and monitoring data from InBusiness and the endline of the RCT will be reviewed to explore the implementation fidelity, mechanisms of impact and contextual factors that can affect variations in outcomes. The process evaluation will use the Medical Research Council guidance for process evaluations of complex interventions as a framework [13].

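### The 199 per arm matches a one-sided 5% test; a conventional two-sided 5% analysis has about 70% power for the 10% effect, not the stated 80%

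*Protocol article*

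**What the plan says.** The Sample size section of the protocol article bases the calculation on household expenditure per capita, one of the two primary outcomes. Its inputs are:

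- Mean: "we assume an average household per capita expenditures of 7811 KSH".
- SD: the source report gave none, so "we assume standard deviation of 40% of the mean (3124 KSH").
- Error rates: "With power of 80% and type 1 error of 5" per cent.
- Effect and result: "we would need a total sample size of 398 (199 per arm) to detect an effect change of 10% of household expenditure per capita".

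The section does not say whether the 5% is one-sided or two-sided, and it uses no baseline correlation. The Design section calls the study an "individual, superiority RCT of the LftW-led component of the InBusiness programme", which does not settle the number of sides. The Data analysis section plans differences in means, followed by linear regression adjusted for the baseline outcome, stratification variables and imbalanced covariates. It does not mention a one-sided test.

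**The concern.** An unqualified 5% type 1 error in a superiority trial is normally read as two-sided. On that reading the section's inputs do not lead to 199 per arm; they lead to about 50 more in each arm. The gap is too large to be rounding.

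This is the only sample size calculation in the article, and it concerns a primary outcome. The Discussion warns that some impacts, particularly subgroup analyses, may be underpowered. It does not say that the main comparison falls short of its stated power. A null result on household consumption would therefore be read as coming from a trial with a 20% chance of missing a 10% gain. The Discussion also expects the results to inform continued investment and scale-up. If the sidedness is still open when endline data arrive, the choice of test could be made after seeing them.

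**Working it through.** **Inputs (protocol article, Sample size):** mean 7811 KSH; SD 3124 KSH; difference 10% × 7811 = 781.1 KSH; power 80%; alpha 5%; equal arms.

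Standardised difference: d = 781.1 / 3124 = 0.250.

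**1. Reproducing the plan's figure.** Normal approximation: n per arm = 2(z_α + z_β)² / d², with z_β = 0.8416.

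| Test | z_α | Normal approximation, n per arm | t-test, n per arm | Total (t-test) |
|---|---|---|---|---|
| One-sided 5% | 1.645 | 197.8 → 198 | 198.5 → **199** | **398** |
| Two-sided 5% | 1.960 | 251.1 → 252 | 252.1 → 253 | 506 |

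The one-sided t-test reproduces both 199 and 398 exactly. The two-sided test does not.

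**2. Other two-sided readings at 80% power (normal approximation).** An SD of 40% of each arm's own mean needs 278 per arm. A log-scale analysis with a coefficient of variation of 0.4 needs 257. Alpha of 0.025 needs 305. All are further from 199.

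**3. Power at 199 per arm, unadjusted.** d√(199/2) = 2.494.

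- Two-sided: Φ(2.494 − 1.960) = Φ(0.534) = 0.703; t-test 0.701.
- One-sided: Φ(2.494 − 1.645) = Φ(0.849) = 0.802; t-test 0.801.

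**4. Effect detectable with 80% power, two-sided, 199 per arm.** Normal approximation: (1.960 + 0.8416) × √(2/199) × 3124 / 7811 = 11.2% of the mean; t-test 11.3%.

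**5. Shortfall.** 504 − 398 = 106 evaluable people, and 106 / 504 = 21%.

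**6. Effect of baseline adjustment.** For a baseline-endline correlation r, the residual SD is 3124√(1 − r²). The article gives no r, so these values are assumptions. Two-sided power (t-test) at 199 per arm:

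| r | 0 | 0.3 | 0.4 | 0.46 | 0.5 | 0.6 |
|---|---|---|---|---|---|---|
| Power | 70% | 74% | 77% | 80% | 82% | 87% |

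If the 495 participants in the Abstract lose 20 to cohort 2 and then 20% to follow-up, (495 − 20) × 0.8 = 380 remain, or 190 per arm if the arms stay equal. The r needed for 80% power is then about 0.50.

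**7. Sensitivity to the assumed SD.** This is separate from the arithmetic error. With illustrative SDs of 50% or 60% of the mean, unadjusted two-sided power at 199 per arm is 51% or 38%.

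**The case against.** The strongest reply has three parts.

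**The one-sided origin is inferred.** This is true, because the article never states the sidedness. A two-sided 5% test with 70% power also gives 199 per arm, as does a two-sided 10% test with 80% power. However, 70% contradicts the stated 80%, and a two-sided 10% test is the one-sided 5% test under another name. A two-sided 5% test with 80% power would also reach about 199 if a correlation of about 0.46 (ANCOVA) or 0.60 (change score) had been used, but none is declared. A one-sided test is therefore the only reading that fits the stated 80% and 5% without an added assumption. The fault does not depend on how the figure arose: either the power is misstated, or an assumption that moves the total by more than 100 people is undisclosed.

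**The final analysis is baseline-adjusted, so 70% is not its power.** This stands as a qualification. The 70% applies to the unadjusted comparison. Power under the planned regression may lie above or below 80%, depending on a correlation the article does not give. The Sample size section takes no credit for adjustment, so this does not explain its figure.

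**Recruitment is finished and no estimate changes.** This is also true, and it is why the remedy is a restatement. It does not make the printed power correct. Nor is the matter simply one for the analysis plan: the article itself prints a power and a sample size that disagree under the conventional reading.

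**Conclusion.** The concern holds. On the article's own mean, SD and effect, 199 per arm gives 80% power only if the 5% is one-sided, which is nowhere declared. With a conventional two-sided 5% test, unadjusted power is 70%, the chance of missing a true 10% gain is about 30%, and 80% power is reached only for an effect of 11.3% of the mean. The shortfall is 106 evaluable people against 504.

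These figures assume equal arms, the stated SD of 40% of the mean, a two-sided test and no baseline adjustment. Baseline adjustment could close the gap if the baseline-endline correlation is about 0.46 or higher. The power of a primary outcome is misstated and must be corrected, although the correction is only to the text.

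**What to change.** Do not enrol more participants. Restate the calculation in the Sample size section, the registry entry and the detailed analysis plan promised before endline:

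1. State that the test is two-sided at 5%, and that 199 per arm gives 70% power for a 10% difference, or 80% power for 11.3%, unadjusted.
2. Credit the baseline-adjusted regression in the Data analysis section by showing power for baseline-endline correlations from 0.3 to 0.6. Say that about 0.46 is needed for 80% at 199 per arm, and about 0.50 at 190 per arm.
3. Before endline, replace the assumed 40% SD with the SD observed in the March 2023 baseline survey, and recompute.

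If a one-sided 5% test was intended, it must be declared and justified before endline data are seen.

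The cost is a reworded paragraph and a registry and analysis-plan update. The stated power becomes less favourable; no participant or data collection is affected.

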**Methods:**

The randomised controlled trial will involve 495 microentrepreneurs who have been verified as eligible for InBusiness by programme implementers. Individuals will be randomised within counties, either being invited to enrol in InBusiness in March 2023 or allocated to a control group. Participants in the control arm will receive information about compliance with business-related laws and available social protection programmes. The trial will assess the impact of InBusiness on household consumption and individual economic empowerment (primary outcomes) as well as food security, well-being, social attitudes, unmet need for disability-related services and microenterprise profits (secondary outcomes). Baseline was conducted in March 2023, and follow-up will be 24 months from baseline (12 months from completion of the programme). Analysis will be through intention to treat. A process evaluation will explore fidelity, mechanisms of impact and the role of context, and complementary qualitative research with participants will be used to triangulate findings across the trial.

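### The recruitment target of 497 covers the 20% loss to follow-up but not also the 20 switches it claims to allow for; minor, about 2 points of power

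*Protocol article*

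**What the plan says.** The Sample size section of the protocol article plans on household expenditure per capita, one of the two primary outcomes. It takes a mean of 7811 KSH and a standard deviation of 3124 KSH, with 80% power and 5% type 1 error, "to detect an effect change of 10% of household expenditure per capita". The result is given as "we would need a total sample size of 398 (199 per arm").

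It then moves from evaluable to recruited numbers: "Assuming a loss to follow-up of 20% and a potential switch of 20 individuals from control group to cohort 2", the latter excluded from the analysis, "we will need to recruit at least 497 individuals". So 497 is presented as meeting both allowances.

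Two other places bear on this. The abstract (Methods) gives the trial size: "The randomised controlled trial will involve 495 microentrepreneurs who have been verified as eligible for InBusiness". The Recruitment and randomisation section describes the switch as a contingency. If cohort 2 has a small number of dropouts (fewer than 20), the implementer may fill the places from randomly chosen controls, who then leave the analysis.

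**The concern.** Dividing 398 by 0.80 already gives 497.5. If the 20% loss by itself accounts for the whole target, nothing is left for the 20 exclusions that the same sentence says are covered. The abstract's 495 is also 2 below the stated minimum, so there is no reserve elsewhere.

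At stake is whether the evaluable number behind the stated 80% power is delivered under the plan's own assumptions. It also matters for conduct. Someone deciding whether to move controls into cohort 2 would read this paragraph as saying that the loss of 20 has been budgeted for.

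**Working it through.** **Inputs** (Sample size section unless noted): mean 7811 KSH; standard deviation 3124 KSH; difference 10% of the mean = 781.1 KSH; power 80%; type 1 error 5%, sidedness not stated; 199 per arm, 398 in total; loss 20%; switches 20; target 497. Trial size 495 is from the abstract.

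**1. Reproduce 398.** Per arm, n = 2 × (SD/difference)² × (z for alpha + z for power)².
- One-sided 5%: 2 × (3124/781.1)² × (1.645 + 0.842)² gives 198 per arm. The t-test version gives 198.5, rounded up to 199. This matches the protocol.
- Two-sided 5%: 252 per arm, 504 in total. This does not match.

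**2. Reproduce 497.** Two routes reach it.
- 398/0.8 = 497.5: correct inflation for the loss, with no allowance for switches.
- 398 × 1.2 + 20 = 497.6: includes the 20, but multiplying by 1.2 does not offset a 20% loss.

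The protocol does not say which was used.

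**3. What 497 delivers.**
- Loss only: 497 × 0.8 = 397.6, in effect 398.
- 20 switch, then 20% of the rest are lost: (497 − 20) × 0.8 = 381.6.
- 20% of all are lost, then 20 of those remaining are excluded: 497 × 0.8 − 20 = 377.6.

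**4. What covering both would need.**
- Switch, then loss: 398/0.8 + 20 = 517.5, so 518.
- Loss, then switch: (398 + 20)/0.8 = 522.5, so 523.

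**5. What 495 delivers.**
- No switches: 495 × 0.8 = 396, 2 short of 398.
- 20 switches: (495 − 20) × 0.8 = 380, or 495 × 0.8 − 20 = 376; 18 to 22 short.
- 19 switches, the most that the Recruitment and randomisation limit allows: (495 − 19) × 0.8 = 380.8, so that limit does not close the gap.

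**6. Power for a 10% difference.** Equal arms are assumed at randomisation, as in the protocol's own calculation, with the switches taken from control. Power = Φ(781.1/SE − z), where SE = 3124 × √(1/n₁ + 1/n₂).

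| Evaluable (intervention, control) | One-sided 5% | Two-sided 5% |
|---|---|---|
| 199, 199 (as planned) | 80.2% | 70.3% |
| 198, 182 (380 in total) | 78.5% | 68.3% |
| 198, 178 (376 in total) | 78.1% | 67.8% |

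Example for 198 and 182: SE = 3124 × √(1/198 + 1/182) = 320.8 and 781.1/320.8 = 2.435. One-sided, Φ(2.435 − 1.645) = 78.5%; two-sided, Φ(2.435 − 1.960) = 68.3%.

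**The case against.** The strongest case is that this hardly matters, and much of that case stands.

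- **The switch may not happen.** It is conditional on dropout from cohort 2. With none, 495 gives 396, and a shortfall of 2 has no practical effect. This stands, and it rules out the reading that 398 will certainly be missed. It does not rescue the sentence, which takes 20 switches as a planning assumption and says that 497 allows for them.
- **The 20 may have been added.** A reader might infer that they were forgotten. The documents do not support that, because 398 × 1.2 + 20 also gives 497. What can be said is what 497 delivers, and on either route it does not deliver 398 after both allowances.
- **Baseline adjustment could make up the loss.** The Data analysis section plans regression on the baseline level of the outcome, which the sample size ignores. If residual variance falls by the factor 1 − r², a baseline-endline correlation r with 1 − r² = 380/398, about 0.21, would offset the loss of 18 people. The protocol gives no correlation, so this is a plausible mitigation and not a figure to rely on. It also leaves the stated arithmetic wrong.
- **Recruitment is over.** Trial status puts its end at 24 March 2023, so the number cannot be raised. That limits the remedy to wording.

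**Conclusion.** The point holds as a minor arithmetic error. The target of 497 yields 398 evaluable only if nobody switches; meeting both stated allowances needs about 518 to 523. With the 495 in the abstract, about 376 to 380 are evaluable if 20 switch and 396 if none do. The cost is about 2 points of power: from 80% to about 78% one-sided, or from about 70% to about 68% two-sided. These figures rest on the protocol's own mean, standard deviation, 20% loss and equal arms, without baseline adjustment.

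Two stronger readings should be resisted.

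- A reader might set 68% against the stated 80% and blame this error for the whole drop. Most of that gap arises because 398 reproduces only with a one-sided test, which is a separate matter.
- A reader might combine the 776 eligible people, the roughly 480 places and the 495 in the trial to infer markedly unequal arms and lower power still. The number of places is approximate, the county quotas are not given, the flow diagram is not shown, and people verified as eligible may have dropped out before baseline. The documents do not establish the arm sizes.

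**What to change.** Reword the end of the Sample size section; no further recruitment or change of design is needed.

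- State that 497 covers the 20% loss to follow-up only, and remove the claim that it also covers the switches.
- State that with 495 randomised and 20% loss, about 396 are evaluable with no switches and about 376 to 380 with 20.
- Give the resulting power for a 10% difference, say whether the test is one- or two-sided, and use the arm sizes actually randomised.
- If a gain from baseline adjustment is quoted, label the correlation as an assumption and show a range.

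The cost is one rewritten paragraph and a slightly less favourable stated power. The benefit is that any decision to move controls into cohort 2 is taken knowing that the sample holds no reserve for it.
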